### Safety outcomes

2.6

Safety outcomes will assess postoperative adverse reactions including, allergy, wound infection, lightheadedness, headache, circumoral numbness, tongue paresthesia, drowsiness, irritability, hypotension, hypertension, hypoventilation, bradycardia, tachycardia, arrhythmia, and cardiac arrest.

### Randomization and blinding

2.7

This open-label, three-arm randomized trial allocated 201 participants in a 1:1:1 ratio (LB, R-P, and P groups; *n* = 67 per group). The open-label design was implemented due to fundamental differences in postoperative pain management protocols among the three study groups. Both investigators and participants were unblinded to treatment assignments to facilitate protocol-specified adjustments in postoperative pain management. Postoperative outcome assessments were conducted by trained nurses who were not involved in the intervention process to minimize potential bias.

### Anaesthetic and study interventions

2.8

All patients fast for at least 8 h and abstain from water for 4 h preoperatively. In the operating room, after establishing a peripheral intravenous channel, they inhale oxygen at 5 L/min via mask, with continuous monitoring of vital signs: non-invasive blood pressure, percutaneous arterial oxygen saturation (SpO_2_), heart rate, and respiratory rate. Preoperatively, all parturients will receive combined spinal-epidural anesthesia. The parturient will be placed in the lateral decubitus position. Following standard aseptic skin preparation and draping with a sterile aperture sheet, subarachnoid blockade will be performed. At the L2/3 or L3/4 interspace, 10–14 mg of 0.5% ropivacaine will be administered intrathecally to achieve rapid onset of surgical anesthesia. An epidural catheter will then be inserted for subsequent intraoperative supplementation if required. In case of inadequate block height or duration, incremental boluses of 2% lidocaine (3-5 mL) or 1% ropivacaine (5 mL) will be administered through the epidural catheter, with careful titration based on the patient’s response and hemodynamic status. Continuous monitoring will be maintained for signs of local anesthetic systemic toxicity, such as tinnitus, perioral numbness, or altered mental status. For parturients with extreme body habitus or height (affecting drug distribution and blockade levels), local anesthetic dosing will be precisely calibrated based on individual anthropometric measurements to optimize analgesic efficacy and safety. Dosing will be precisely calibrated in accordance with each patient’s anthropomorphic measurements to ensure optimal analgesic outcomes. Upon verification of both the requisite analgesic level (at least T6) and the efficacy of the blockade, the cesarean section will be initiated. Supine hypotensive syndrome and total spinal anesthesia are medical emergencies requiring immediate treatment, so, intensive monitoring during the surgical procedure and maintaining hemodynamic stability with the utilization of vasoactive medications as needed to support vital sign parameters are essential. All patients will receive postoperative analgesic regimens as dictated by the sealed-envelope protocol. This information is exclusively known to the anesthesiologist administering the anesthesia, with all other individuals involved remaining blinded to the details. Participants in group LB will receive bilateral QL nerve block [posterior QL block (20)] utilizing liposomal bupivacaine injection under ultrasound guidance (Liposomal bupivacaine injection, 133 mg per 20 mL on each side); participants enrolled in group R-P will receive bilateral QL nerve block utilizing ropivacaine injection under ultrasound guidance (Ropivacaine injection, 20 mL of 0.375% ropivacaine on each side), in conjunction with a PCIA; and participants enrolled in group P will be managed with standard PCIA, without supplementary nerve block interventions. In the preparation of PCIA pumps, each total volume is standardized at 100 mL, and the formulation includes sufentanil and 8 mg of ondansetron. The total amount of sufentanil is calculated based on a dosage of 2 μg per kilogram of body weight. The background infusion rate is set within the range of 0.04 μg/kg/h. The PCIA protocol is set with a 0.04 μg/kg bolus dose and a 15-min lockout interval to ensure safety.

This study will establish an emergency analgesia team to promptly address urgent and intolerable pain, ensuring swift relief for patients. The acute pain management protocol will incorporate paracetamol and oxycodone; initially, intravenous paracetamol 1 g will be administered every 6 h as needed, with a maximum daily dose not exceeding 4 g. If patients continue to report intolerable pain (a VAS pain score > 4) for more than 30 min, or if the maximum daily dose of paracetamol has been reached, oral oxycodone 5 mg will be subsequently employed, with dose adjustments made within the safe dosage range as appropriate. Repeat doses will be given at 4–6 h intervals, with careful monitoring, and dose adjustments within safe limits.

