Circumoral numbness			×	×	×	×	×	
Tongue paresthesia			×	×	×	×	×	
Drowsiness			×	×	×	×	×	
Irritability			×	×	×	×	×	
Hypotension			×	×	×	×	×	
Hypertension			×	×	×	×	×	
Hypoventilation			×	×	×	×	×	
Bradycardia			×	×	×	×	×	
Tachycardia			×	×	×	×	×	
Arrhythmia			×	×	×	×	×	
Cardiac arrest			×	×	×	×	×	

According to SPIRIT, statement of defining standard protocol items for clinical trials.

Pre-op, preoperative; Post-op, postoperative; QoR-15, patient self-assessment of Quality of Recovery-15 scale; VAS, visual analogue scale; NRS, numerical rating scale; PCIA, patient-controlled intravenous analgesia pump.

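### The scheduled safety items in 2.6 and Table 1 omit tinnitus and only partly cover altered mental status, both of which section 2.8 names as signs of local anesthetic toxicity

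*Protocol article*

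**What the plan says.** Three places in the protocol article bear on this.

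- **Section 2.8 (Anaesthetic and study interventions)** provides for epidural supplementation if the block is inadequate: "incremental boluses of 2% lidocaine (3-5 mL) or 1% ropivacaine (5 mL) will be administered through the epidural catheter". The next sentence reads: "Continuous monitoring will be maintained for signs of local anesthetic systemic toxicity, such as tinnitus, perioral numbness, or altered mental status". The three signs are given as examples.
- **Section 2.6 (Safety outcomes)** sets out what is assessed after surgery: "Safety outcomes will assess postoperative adverse reactions including, allergy, wound infection, lightheadedness, headache, circumoral numbness, tongue paresthesia, drowsiness, irritability", followed by "hypotension, hypertension, hypoventilation, bradycardia, tachycardia, arrhythmia, and cardiac arrest". That makes 15 items. The abstract gives the same 15.
- **Table 1 (section 2.9)** has an adverse-event row for each of these 15, including "Circumoral numbness", "Tongue paresthesia" and "Irritability", each marked at 0, 12, 24, 48 and 72 h. It shows no row for other events.

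Section 2.9 also requires any serious adverse event to be reported promptly to the principal investigator, related to study medication or not, and to the Data Monitoring Committee within 24 hours.

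**The concern.** The safety list plainly aims to pick up local anesthetic toxicity, since circumoral numbness and tongue paresthesia are on it. Yet it has no item for tinnitus, which the protocol itself names as such a sign, and no general item for altered mental status.

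Section 2.8 speaks of the intraoperative epidural boluses, but these are signs of a drug class and not of one route. Groups LB and R-P then receive a bilateral local anesthetic injection, scheduled in Table 1 at 0 h. The Discussion describes the liposomal product as acting for at least 72 h. The 0 to 72 h assessments are therefore where toxicity from the block would be recorded.

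What is at stake is the completeness of the safety description. The Discussion says that clinical data on liposomal bupivacaine in bilateral quadratus lumborum blocks are lacking and hypothesizes improved safety, and the Conclusion promises evidence on safety. An item that is not asked about on a fixed schedule tends to be recorded unevenly or not at all.

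**Working it through.** The article gives no rate or figure on this point to reproduce, so the check is a term-by-term comparison.

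| Sign named in 2.8 | Item in 2.6 | Row in Table 1 | Coverage |
|---|---|---|---|
| Perioral numbness | Circumoral numbness | Same, at 0, 12, 24, 48, 72 h | Full (synonym) |
| Altered mental status | Drowsiness; irritability | Same, at 0, 12, 24, 48, 72 h | Partial: no item for confusion or disorientation |
| Tinnitus | None | None | None |

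**Step 1. Do 2.6 and Table 1 agree?** Yes, on all 15 items. The omission is not a slip in one of the two places.

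**Step 2. Is the list left to another document?** The article prints it in the abstract, in 2.6 and in Table 1, with visit times for every item in the table. It presents a worked-out item set, and the gap is visible in what is printed.

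**Step 3. Which patients are affected?** Those who meet all of these conditions: the sign is tinnitus, or a mental change other than drowsiness or irritability; the event is not serious; and no other listed sign is present (for example circumoral numbness, tongue paresthesia, lightheadedness or arrhythmia). A patient with a further listed sign is recorded under that sign, and a serious event is reported under 2.9.

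**Step 4. What could one or two such patients mean for an arm?** The documents give no frequency, so this is illustration only. With 67 per arm, one patient is 1/67 = 1.5 percentage points. Exact (Clopper-Pearson) 95% limits:

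- 0 of 67: the upper limit solves (1 − p)^67 = 0.025, so p = 1 − 0.025^(1/67) = 5.4%.
- 2 of 67: 2/67 = 3.0%. The limits solve P(X ≥ 2) = 0.025 and P(X ≤ 2) = 0.025, giving 0.4% to 10.4%.

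If two patients in an arm had isolated tinnitus and neither was recorded, the report would show 0% (up to 5.4%) where 3.0% (0.4% to 10.4%) was true. The intervals overlap widely. The example shows the resolution of an arm of 67 and does not predict what will happen.

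**The case against.** The strongest reply is that the two lists serve different purposes. The sentence in 2.8 tells the anesthesiologist what to watch for during neuraxial anesthesia, before surgery begins, and offers examples. Section 2.6 lists postoperative reactions. A bedside vigilance list and an outcome list need not match. This stands: a reader might infer that 2.8 and 2.6 contradict each other, and they do not. The point is a gap in coverage.

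Three further replies have force.

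- **Event-free status.** A reader might infer that a patient with only tinnitus would be counted as free of adverse events. The article does not support that. Section 2.6 presents its items as inclusions, no event-free status or composite is defined, and nothing says that unlisted events go unrecorded. Case report forms are mentioned in 2.9 but not shown, and they may have a free-text field.
- **Direction of bias.** A reader might infer that the gap makes the blocks look safer than they are. The documents do not establish this. All arms receive intrathecal ropivacaine and may receive epidural lidocaine or ropivacaine, so Group P is exposed to local anesthetic too. Groups R-P and P also receive sufentanil, which can alter mental status, so a missing item could equally hide events in those arms.
- **Existing coverage.** The list already holds several toxicity signs at five time points, and serious events have their own route. Only isolated, non-serious signs are exposed.

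None of this removes the remaining point: tinnitus has no scheduled item, and confusion has none.

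**Conclusion.** The point holds as a minor gap that is cheap to close. Of the three example signs in 2.8, one is scheduled, one is scheduled in part and one is not scheduled. Isolated, non-serious tinnitus or confusion after the block may therefore go unrecorded.

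The size cannot be estimated from the documents. Each missed patient is 1.5 percentage points of an arm, and the primary outcome and its test are unaffected.

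The conclusion assumes that the printed rows of Table 1 are the items asked at each assessment. If the full case report form already asks about tinnitus and confusion, or prompts for other events at each visit, the remedy reduces to bringing the article's list into line with it.

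**What to change.** Add tinnitus and confusion/altered mental status to 2.6 (and to the matching list in the abstract) and as two rows in Table 1 at the existing 0, 12, 24, 48 and 72 h assessments. Report both by arm with the other adverse events.

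A summary of any sign of local anesthetic systemic toxicity by arm, with exact confidence intervals, is optional. If it is used, fix its components in advance and state that opioids can also change mental status, since Groups R-P and P receive sufentanil by pump and rescue oxycodone may be given.

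The cost is two more form items at assessments that already take place and the corresponding table rows. It needs no extra visit and leaves treatment, sample size and the primary analysis unchanged.

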### Secondary outcomes

2.5

Secondary outcomes will include patient self-assessment of the Quality of Recovery-15 (QoR-15) scale at 24 and 48 h postoperatively, as well as Visual Analog Scale (VAS) pain scores at rest, recorded at 12, 24, 48, and 72 h post-surgery. Additionally, the number of postoperative acute analgesic requests will be documented. Postoperative anxiety regarding the hypothetical repeat cesarean section will be assessed at 72 h post-surgery using the VAS score (scores range from 0 to 10, with 0 indicating the best and 10 indicating the worst, named VAS anxiety score) (19). Subjective sleep quality will be evaluated for 24, 48, and 72 h post-surgery using the Numerical Rating Scale (NRS) (scores range from 0 to 10, with 0 indicating the worst and 10 indicating the best sleep quality). The maximum walking duration, defined as the longest duration a patient can walk after surgery, will be measured at 24, 48, and 72 h post-surgery. Patient satisfaction with analgesic management will be assessed at 24, 48, and 72 h post-surgery using the NRS (scores range from 0 to 10, with 0 indicating the worst and 10 indicating the best). Postoperative opioid use (including sufentanil via PCIA and any rescue oxycodone) will be recorded over the 0–72 h period. For comparability, all opioid doses will be converted to intravenous morphine milligram equivalents (MME) using standard equianalgesic conversion factors. Both the raw consumption of sufentanil and oxycodone as well as the total MME will be reported. Furthermore, the incidence of nausea and vomiting and length of hospital stay will be recorded.

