### Data collection and monitoring

2.9

Data collection will encompass a range of patient characteristics, including age, height, weight, body mass index (BMI), ASA score, drinking status, smoking status, parity, duration of surgery, intraoperative bleeding, and intraoperative analgesia grade. All pertinent data will be meticulously recorded in case report forms (CRFs) and subsequently inputted into an electronic database under the vigilant supervision of the principal investigator (Table 1). An independent Data Monitoring Committee (DMC) will be tasked with the ongoing oversight of the data collection process. Upon completion of data registration, the electronic database will be safeguarded. De-identified datasets will then be forwarded to an independent statistician for comprehensive analysis in accordance with a predefined statistical plan. Any serious adverse events (SAEs), whether or not they are related to the study medication (e.g., persistent hemodynamic instability), must be promptly reported to the principal investigator. In such instances, the perioperative care team is obligated to implement necessary measures to safeguard participant wellbeing. Furthermore, these SAEs must be communicated to the DMC within a 24-h window for thorough discussion and to determine if any adjustments to the study interventions or the study’s discontinuation are warranted.

**Table 1 tab1:** Schedule of patient enrolment, study interventions and outcome assessment.

	Study period							
	Enrollment	Allocation	Post-allocation					Close-out
Time point	Pre-op visit	Pre-op 1 day	0 h post-op	12 h post-op	24 h post-op	48 h post-op	72 h post-op	Discharged
Patient enrolment								
Eligibility criteria	×							
Written informed	×							
Consent								
Demographic data	×							
Baseline characteristics	×							
Randomization/allocation		×						
Study interventions								
Liposomal bupivacaine			×					
Ropivacaine & PCIA			×					
PCIA			×					
Outcome assessment								
VAS pain score during turning over				×	×	×	×	
VAS pain score at rest				×	×	×	×	
QoR-15 scale					×	×		
Need for rescue analgesia				×	×	×	×	
VAS anxiety score							×	
NRS sleep score					×	×	×	
Maximum walking duration					×	×	×	
NRS for satisfaction with analgesic					×	×	×	
Opioid consumption								×
Length of hospital stay								×
Nausea			×	×	×	×	×	
Vomiting			×	×	×	×	×	
Adverse events								
Allergy			×	×	×	×	×	
Wound infection			×	×	×	×	×	
Lightheadedness			×	×	×	×	×	
Headache			×	×	×	×	×	

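### As printed, one PCIA pump is empty by 50 h, so without a refill or removal well before 48 h the 0–72 h sufentanil total cannot reflect demand in R-P or P (minor)

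*Protocol article*

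**What the plan says.** All settings are in section 2.8 of the protocol article and are the same for the two pump arms, R-P and P. On volume: "each total volume is standardized at 100 mL". On load: "The total amount of sufentanil is calculated based on a dosage of 2 μg per kilogram of body weight". On background: "The background infusion rate is set within the range of 0.04 μg/kg/h". On demand doses: "The PCIA protocol is set with a 0.04 μg/kg bolus dose and a 15-min lockout interval to ensure safety". LB has no pump. The article prints no rule for refilling the pump, replacing it or taking it down.

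Section 2.5 says that opioid use, covering PCIA sufentanil and rescue oxycodone, "will be recorded over the 0–72 h period", and adds: "Both the raw consumption of sufentanil and oxycodone as well as the total MME will be reported". In Table 1 (section 2.9) the row "Opioid consumption" is marked once, at discharge. Section 2.11 treats sufentanil consumption as a continuous variable with one time point, compared by t-test or Mann–Whitney U. It also states that secondary outcomes are exploratory and not corrected for multiplicity.

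**The concern.** The load and background in section 2.8 do not fit the window in section 2.5. The background infusion alone uses up the load well before 72 h, and boluses only bring that moment forward. A total read after the pump has run dry equals the load. It does not show how much the patient asked for.

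R-P v P is the only sufentanil comparison between two arms that both have a pump. If both totals are fixed at the same μg/kg, a nil difference could be taken as evidence that the ropivacaine block spares no opioid, when the pump settings had decided the result. For LB v P and LB v R-P, the sufentanil part of the difference is likewise set by design: none in LB against a full pump in the other arm.

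**Working it through.** **Inputs (section 2.8):** load 2 μg/kg in 100 mL; background 0.04 μg/kg/h; bolus 0.04 μg/kg; lockout 15 min, so at most 4 boluses per hour. **Window (section 2.5):** 0–72 h. The article states no pump duration or expected total, so there is no figure of its own to reproduce.

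**Consistency of the settings.** 2 μg/kg in 100 mL is 0.02 μg/kg per mL. The background is therefore 0.04/0.02 = 2 mL/h and one bolus is 2 mL. These round values support reading 0.04 as a single rate despite the loose wording about a range.

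**Time to empty** = load / (background + boluses per hour × bolus dose):
- no boluses: 2/0.04 = 50 h
- 0.5 per hour: 2/0.06 = 33 h
- 1 per hour: 2/0.08 = 25 h
- lockout maximum of 4 per hour: 2/0.20 = 10 h

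Background alone over 72 h would need 0.04 × 72 = 2.88 μg/kg, which is 144% of the load. Every term is per kg, so body weight drops out.

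**Attainable cumulative dose from one pump at time t.** Lower limit = min(2, rate × t). Upper limit = min(2, (rate + 4 × 0.04) × t), which is 2.00 at every time below.

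| Background (μg/kg/h) | 12 h | 24 h | 48 h | 72 h |
|---|---|---|---|---|
| 0.04 (printed) | 0.48–2.00 | 0.96–2.00 | 1.92–2.00 | 2.00 |
| 0.03 (assumed) | 0.36–2.00 | 0.72–2.00 | 1.44–2.00 | 2.00 |
| 0.02 (assumed) | 0.24–2.00 | 0.48–2.00 | 0.96–2.00 | 1.44–2.00 |

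At the printed rate, the room left for boluses is (2 − 0.96)/0.04 = 26 at 24 h, (2 − 1.92)/0.04 = 2 at 48 h, and none at 72 h. The 72 h total is fixed at any rate of 2/72 = 0.0278 μg/kg/h or above.

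**Raw μg.** After run-out the raw total is 2 × body weight: 120 μg at 60 kg, 180 μg at 90 kg. With an assumed weight SD of 10 kg and 67 × 0.9 ≈ 60 patients per arm, the SD is 20 μg and the standard error of the R-P v P difference is 20 × √(2/60) = 3.65 μg. All of that is body weight.

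**What an earlier reading could show.** This part rests on assumed demand, because the documents give none. Bolus counts by 24 h are gamma-Poisson with a between-patient CV of 0.6 to 1.0, and demand halves in each later 24 h period. There are 60 patients per arm, compared by Mann–Whitney at two-sided 0.05, since section 2.11 applies no multiplicity correction to secondary outcomes.

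| Mean boluses by 24 h, P v R-P | 24 h difference, CV 0.6 to 1.0 | 24 h power, CV 0.6 to 1.0 | 72 h difference per kg |
|---|---|---|---|
| 12 v 6 | 0.23 to 0.18 μg/kg | about 99.9% to 87% | exactly 0 |
| 12 v 9 | 0.11 to 0.08 μg/kg | about 57% to 25% | exactly 0 |

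Raw μg at 72 h rejects only at about the nominal 5% in these runs.

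**The case against.** **The premise is not printed.** The fixed total needs one pump per patient, run to empty. The article says how a pump is prepared, not how long it stays or whether it is refilled. Section 2.7 mentions adjustments to postoperative pain management set by the protocol, and a condensed article may leave pump handling to the full protocol. This stands as a condition on the claim, and the missing rule is not itself a fault. It does not remove the point: section 2.7 does not mention the pump, removal at 48 h still leaves a spread of only 0.08 μg/kg, and a background as low as 0.0278 still empties the pump by 72 h.

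**The contrast is not a key question.** The Discussion poses LB v P and LB v R-P. R-P v P is not singled out, and section 2.11 names no pairs for sufentanil. This stands, and it lowers the weight of the point.

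**The opioid outcome is wider than pump sufentanil.** Total MME includes rescue oxycodone, and Table 1 records the need for rescue at 12, 24, 48 and 72 h. This also stands. A reader might infer that the opioid outcome as a whole is uninformative, or that the main pain result is compromised. The documents support neither. Rescue use can still separate the arms, and the primary analysis uses VAS scores on movement, which do not depend on the sufentanil total.

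**Conclusion.** The point holds in conditional form and is minor. The exhaustion time and the fixed 72 h total follow from printed figures alone. They assume a background of 0.04 μg/kg/h and no refill or removal well before 48 h. Under those conditions the R-P v P sufentanil comparison is decided before any patient presses the button, and the raw version compares body weights.

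The damage is limited to one component of an exploratory secondary outcome. The power figures for a 24 h reading depend on assumed bolus counts and CVs and are only illustrative. It would go too far to say that the trial cannot assess opioid sparing: it cannot do so through the 72 h sufentanil total on these settings.

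**What to change.** 1. Keep the 0–72 h sufentanil total and total MME as planned.
2. Add cumulative sufentanil delivered by 12 h and 24 h, in μg/kg, from pump readings at the existing visits. Weight is already collected ("age, height, weight, body mass index (BMI"). Use the 24 h value, with a confidence interval, for R-P v P.
3. Record the time of pump exhaustion, refill or removal.
4. State the background rate as one value or as a true range.
5. State in the report that a nil 72 h sufentanil difference is not evidence against sparing, and that the sufentanil part of the LB contrasts is set by design.

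**Cost.** Two readings in each of 67 × 2 = 134 patients, which is 268 readings, plus one line in Table 1 and a log of pump events, some of which will fall between visits. **Limit.** At 24 h the fixed background is still 0.96/1.44 = 67% of the dose after 12 boluses and 0.96/1.20 = 80% after 6, so modest sparing, such as a quarter fewer boluses, may be missed.
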